# Integrated exercise program in opioid agonist therapy clinics and effect on psychological distress: study protocol for a randomized controlled trial (BAReAktiv)

**DOI:** 10.1186/s13063-024-07993-2

**Published:** 2024-02-29

**Keywords:** Opiate substitution treatment, Motor activity, Exercise therapy, Substance-related disorders, Intervention, Outpatient, Behavioral intervention

## Abstract

**Background:**

Substance use disorder is associated with unhealthy lifestyle choices, resulting in adverse social and health consequences. People with opioid use disorder receiving opioid agonist therapy, in particular, have high morbidity and reduced quality of life. Physical activity is recommended as an adjunctive treatment for people with substance use disorder, but there is minimal evidence from randomized controlled trials on the effects of this among people with substance use disorder receiving opioid agonist therapy.

**Methods:**

BAReAktiv is a multicentre randomized controlled trial. The study aims to recruit 324 patients receiving opioid agonist therapy (parallel groups randomized 1:1 to integrated exercise intervention or control, superiority trial). A 16-week group-based integrated exercise intervention with workouts twice a week. The exercise program consists of endurance and resistance training. The target group will be patients 18 years and older receiving opioid agonist therapy in outpatient clinics in several centers in Western Norway. The primary outcome of the study is the effect on psychological distress measured by Hopkins’ symptom checklist with ten items. Secondary outcome measures include physical functioning assessed with a 4-min step test, activity level, fatigue symptoms, quality of life, and changes in inflammation markers. This study will provide improved knowledge on the effects of an integrated exercise program in opioid agonist therapy.

**Discussion:**

Systematically integrating exercise programs for people receiving opioid agonist therapy could lead to a shift towards a stronger focus on health behaviors in outpatient care. Integrating exercise could benefit patient recovery and reduce disease burden. Further scale-up will be considered if the provided exercise program is safe and effective.

**Trial registration:**

ClinicalTrials.gov. NCT05242848. Registered on February 16, 2022.

## Administrative information

Note: The numbers in curly brackets in the protocol refer to SPIRIT checklist item numbers. The order of the items has been modified to group similar items (see: http://www.equator-network.org/reporting-guidelines/spirit-2013-statement-defining-standard-protocol-items-for-clinical-trials/).

###  Background and rationale {6a}

Substance use disorders are associated with unhealthy lifestyle choices, resulting in adverse social and health consequences [1, 2]. People with opioid use disorder have particularly high morbidity, reduced physical fitness and quality of life [3–5], and a higher risk of premature death [6, 7].

Physical activity is defined as any bodily movement produced by skeletal muscles, which requires energy expenditure. Exercise is planned, structured, repetitive, and intentional physical activity intended to improve or maintain physical fitness [8]. Exercise has been suggested as an adjunctive treatment strategy for people with substance use disorder [7], due to its positive effects on health, quality of life, and reducing the burden of substance use disorder patterns [9, 10]. People with opioid dependence receiving opioid agonist therapy (OAT) often have significant mental health problems and calls for improved mental and physical health assessment and patient care [11, 12]. Physical activity and exercise can be effective adjunctive treatment methods for reducing nicotine, alcohol, and drug use [7, 13, 14]. Still, we need more knowledge about the effects of exercise as part of OAT, and how to best integrate an exercise program into OAT [15]. Few studies have investigated the effects of an exercise program on OAT patients [16–21], and none of these are randomized controlled trials with power to assess effects. Results from these studies suggest that exercise interventions could be desirable on physical fitness [19], substance use [16], and quality of life [19]. However, the potential effect is uncertain. Further research on exercise intervention would therefore be beneficial [12].

### Objectives {7}

This paper describes the BAReAktiv protocol. The primary objective is to evaluate the effect of a 16-week exercise intervention on the level of psychological distress among people receiving opioid agonist therapy.

We will also assess adherence to physical activity recommendations, physical functioning, symptoms of lung disease, assessment of changes in quality of life, fatigue, and inflammatory markers from a blood sample.

### Trial design {8}

A multicentre individually randomized controlled trial, parallel groups, 1:1 allocation ratio, superiority trial.

## Methods: participants, interventions, and outcomes

This protocol was developed from preliminary experiences from a multicentre pilot study evaluated with a mixed-method design (not yet published). In summary, the ATLAS4LAR study group conducted a 6-week pilot intervention with a group-based exercise program for people receiving OAT. This pilot study was conducted from May 2021 to June 2021. We aim to evaluate a prolonged scaled-up version of this intervention.

### Study setting and participants {9}

Recruitment will take place in OAT outpatient clinics in Bergen and Stavanger, two of the four largest cities in Norway. The Department of Addiction Medicine at Haukeland University Hospital in Bergen and OAT clinic in Stavanger have adopted an integrated treatment and care model for patients receiving OAT. In Bergen, OAT outpatient clinics are established in each district. Staff are multidisciplinary and include a consultant as well as a doctor specializing in addiction medicine, nurses, social workers, and psychologists. The patients are followed up almost daily with an observed intake of the OAT medications, such as methadone and buprenorphine treatment [22]. Bergen has suburb-based outpatient clinics while Stavanger has one main central outpatient clinic in addition to one for the neighboring areas. Except that, they are mostly similar. The treatment model in Bergen and Stavanger is a good platform to test the integration of additional interventions aiming to improve the health of a vulnerable group and gather knowledge, which traditionally has been very difficult to reach [23].

### Eligibility criteria {10}

The participants will be recruited from OAT outpatient clinics in Bergen and Stavanger inclusion criteria are as follows:Adults receiving OAT from the outpatient OAT clinics with weekly follow-ups.Giving informed consent.

Exclusion criteria:Not able to participate in the physical exercise intervention due to health disabilities.Being imprisoned or hospitalized.

### Who will take informed consent? {26a}

Research nurses from the included OAT clinics invited participants to take part in the study during an annual health assessment. Interested participants were asked to provide a written informed consent.

### Additional consent provisions for collection and use of participant data and biological specimens {26b}

Participants consented for participation, review of medical records, and for the collection of blood samples to assess biochemical indicators of inflammation.

## Interventions

### Explanation for choice of comparators {6b}

To reduce selection bias, participants in the intervention and comparison groups are recruited from the same OAT clinics. The comparison group follows standard treatment without offered exercise intervention. Norwegian standard care for OAT patients primarily focuses on opioid substitution with opioid agonist therapy. In contrast, our intervention arm extends this approach by testing the added value of physical activity and how this impacts on mental health.

### Intervention {11a}

The intervention is a supervised group-based exercise intervention for 16 weeks, which includes two outdoor sessions per week. The workout consists of two parts, the first focusing on endurance and the second focusing on resistance training. Every workout follows the same structure and lasts for approximately 45 min. The exercise starts with roughly 15 min of endurance warm-up, followed by moderate to high-intensity running or walking intervals. Eight repetitions of 30 s uphill, and the participants can freely choose between running and walking. The preferred intensity of the intervals is > 13 on Borg-score 20, meaning at least moderate-intensity activity [24]. The participants will be guided in using the Borg scale to identify exercise intensity, and the perceived exertion will be measured at the end of the endurance section. The resistance training consists of four exercises focusing on strengthening the large muscle groups, including pectoralis major, rectus abdominis, quadriceps femoris, gluteus maximus, and latissimus dorsi. The strength-training program follows the same structure as the intervals, 30 s of active time and approximately 60 s of break, four rounds.

The intervention is based on the World Health Organization 2020 guidelines on physical activity [25], and national guidelines for chronic obstructive pulmonary disorder [26]. In addition, a clinical therapist panel and users with extensive experience in exercise as therapy for drug and mental health disorders from Stavanger and Haukeland University Hospitals provided feedback on the intervention. We drew upon the preliminary experiences of patients and research personnel from the pilot study as well. Clinical staff, research staff, and people with user experience will supervise the exercise sessions. The supervisors have been trained to carry out this exercise program, and the research team will provide weekly guidance to these supervisors. Research nurses will perform random checks throughout the intervention period using the Borg-scale 20 [24], to determine whether intervention sessions use the desired intensity, or if any adjustments are needed.

### Criteria for discontinuing or modifying allocated interventions {11b}

If the participant asks to discontinue the allocated interventions, they are free to discontinue the intervention at any time.

### Strategies to improve adherence to interventions {11c}

The intervention will use existing infrastructure to improve adherence to the intervention. We will try to coordinate physical exercise sessions to link as best as possible with the clinical follow-up of the participants including the choice of timing of the session. Short text message reminders will also be sent to participants to ensure they remember the session.

### Relevant concomitant care permitted or prohibited during the trial {11d}

There are no restrictions on concomitant care during the trial.

### Provisions for post-trial care {30}

At their local OAT clinic, participants will receive yearly health assessments following the trial.

### Outcomes measures {12}

The data collection will take place within the patient’s local OAT clinic and the research nurse will lead the collection. The nurse has training in performing these tests, both as part of the annual assessment and in the pilot study.

Primary outcome measure:

Psychological distressThe primary outcome is psychological distress 12–16 weeks after intervention initiation assessed with the Norwegian-validated translation of the ten-item version of the Hopkins Symptom Checklist (SCL-10) [27]. SCL-10 is a valid, reliable, relatively brief, and easy tool to implement for assessing psychological distress symptoms. SCL-10 will be evaluated with mean SCL-10 item score, and compared between the intervention and control arm.

Secondary outcome measures 12 to 16 weeks after intervention initiation:Physical functioning assessed with a 4-min step test measuring the number of steps climbed in the period [28].Physical activity assessed using the Norwegian-validated translation of the International Physical Activity Questionnaire (IPAQ) [29].Changes in fatigue will be assessed with the Fatigue Symptom Scale (FSS-3) [30].Changes in health-related quality of life assessed with EuroQoL EQ-5D-5L [31, 32] in addition to a self-reported question on happiness on a 0 to 10 scale.Changes in self-reported substance use will be assessed comparing change in overall substance use (using a semi-continuous substance use score from 0 to 1 including frequency of intake of several substances) by before intervention and in a 1-year follow-up visit [11].Adherence to OAT (as proportion in each arm who 1 year after initiation of the intervention is receiving OAT with active follow-up during last month).Biochemical indicators of inflammation (measured with C-reactive protein in serum and total leukocyte count in blood).◦ Sub-group (*n* = 60): IFN-gamma, IL-1beta, IL-1RA, IL-6, IL-8, IL-10, IL-17A, MCP-1, TNF-alfa measured in dried blood spots.

Baseline characteristics as predictors for degree of active participation in the physical activity interventions will be assessed.

### Participant timeline {13}

See Table 1: Flow chart of the study outlining follow-up visits and assessment at each visit.

**Table 1 Tab1:** Flow chart of the study outlining follow-up visits and assessments at each visit

	**Screening (research nurse)**	**Treatment follow-up week 0 to 16 (nurses/social workers)**	**Intervention end-assessment (12–16 weeks after initiation)**	**Intervention post-assessment (10–30 weeks after intervention) initiation)**	**Annual follow-up**
**Research nurse assessment**	X		X	X	X
- Informed consent	X				
- Eligibility assessment	X				
- Follow-up by OAT staff		X			
- Clinical assessment	X		X	X	X
Biochemical tests	X		X	X	X
Physical funct. (4-min step test)	X		X	X	X
Physical activity. (IPAQ)	X		X	X	X
Psychological distress (SCL-10)	X		X	X	X
Fatigue symptoms (FSS-3)	X		X	X	X
Quality of life EQ-5D-5L	X		X		X

### Sample size {14}

Based on a cohort study in the same population [11], we assume that psychological distress assessed with a mean item score of SCL-10 score is 2.2 with a standard deviation of 0.8. To detect a reduction in psychological distress to a mean level of SCL-10 of 1.8 which is under the typically used threshold of 1.85 for substantial psychological distress [27], among participants taking active part in intervention and being evaluated among those randomized to intervention groups, with 62.5% of the participants randomized to the intervention assumed to take active part in intervention (i.e., a mean among those randomized to the intervention of 1.95), with 80% power a 1.1 intervention: control ratio, a two-sided test, and alpha (*α)* error of 5%. Based on these assumptions, 324 persons are required in total, including 162 persons in the intervention arm and 162 persons in the control arm (statistical power was calculated in Stata SE 17.0).

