### Methods in analysis to handle protocol non-adherence and any statistical methods to handle missing data {20c}

If any variables are missing of the primary outcome, they will be handled using an intention-to-treat strategy; the baseline value will be used.

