## Discussion

This multicentre randomized controlled trial aims to evaluate the effects of an integrated group-based physical exercise intervention on psychological distress in people with substance use disorders receiving OAT. To the best of our knowledge, no large randomized controlled trials with exercise interventions have been developed and tested among patients receiving OAT [15].

If successful, an exercise program could be integrated into treatment service. Integrated treatment models could be an alternative to increase adherence to OAT and lifestyle-related disorders. However, barriers to succeeding with exercise programs in clinical settings in this population include difficulties with adherence to the exercise program, difficulty devising a suitable intervention, and the relatively high cost of intervention related to personnel, equipment, or facilities [18, 40, 41].

Improving health seems to be one of the most important motives to start exercising for people with opioid use disorders. These findings are important factors to take into account when designing exercise interventions and using an already familiar setting to deliver treatment may lower the participation threshold to increase engagement [42].

Our trial has some limitations and several strengths. As mentioned earlier, complete blinding is hard to achieve. However, we aim to blind the outcome assessor and analyst in this study, and the data collectors have a strict protocol to follow when performing physical function tests [28]. All participants will receive the same instruction, reducing the possibility of external motivation from the data collector performing the 4-min step test. Additionally, since the study is individually randomized, the risk of confounding factors is minimized. The study population receiving OAT is large enough to answer the primary objectives accurately, and the associated accuracy for secondary objectives is assumed to be adequate.

If successful, this approach has the potential for widespread application through health care services for people in opioid agonist therapy.

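### The 80% power at 324 participants holds only if 62.5% of the intervention arm are both active and measured; the protocol defines the 62.5% by activity alone and leaves no margin

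*Protocol article*

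**What the plan says.** All references are to the Protocol article.

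- **Sample size {14}** assumes a "mean item score of SCL-10 score is 2.2 with a standard deviation of 0.8". The target is "To detect a reduction in psychological distress to a mean level of SCL-10 of 1.8", and this applies "among participants taking active part in intervention and being evaluated among those randomized to intervention groups".
- The effect is then diluted over the whole arm, "with 62.5% of the participants randomized to the intervention assumed to take active part in intervention", to give "a mean among those randomized to the intervention of 1.95". With 80% power and a two-sided 5% test, the section concludes that "324 persons are required in total, including 162 persons in the intervention arm and 162 persons in the control arm".
- **Abstract, Methods** gives 324 as the number to recruit.
- **Section {20c}**, on non-adherence and missing data, says that for a missing primary outcome "the baseline value will be used". The sentence is conditional and gives no rate.
- **Section {20a}**, on the primary and secondary analyses, specifies a Gaussian generalized linear model analysed by intention to treat. It allows covariate adjustment only where an imbalance is seen at baseline. SCL-10 is measured at screening (Table 1).
- **Discussion** states: "The study population receiving OAT is large enough to answer the primary objectives accurately".

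**The concern.** The number recruited equals the number that must contribute a full effect, so nothing absorbs missing follow-up scores. The missing-data rule matters here. Scoring an unmeasured but active participant at baseline keeps that person in the analysis and removes their benefit from the arm mean. This costs more power than losing the observation would.

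The sample-size paragraph uses two conditions and quantifies one. The 1.8 belongs to people who are active and evaluated; the 62.5% is described as the share who are active. The two match only if every active participant is measured, or if the 62.5% was meant to cover both conditions. The text does not say which.

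If the trial ends without a significant difference, readers will judge that result against the stated 80%. If real power was nearer 65 to 70%, they would take the null result as stronger evidence of no benefit than it is.

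**Working it through.** **Inputs from Sample size {14}:** control mean 2.2, SD 0.8, mean 1.8 in active and evaluated participants, active share 0.625, 80% power, two-sided 5%, equal arms of 162.

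**Step 1: reproduce the stated figure.**

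- Diluted mean: 2.2 − 0.625 × (2.2 − 1.8) = 2.2 − 0.25 = 1.95, as stated.
- Standardised difference: 0.25 / 0.8 = 0.3125.
- The two-sample t-test needs 161.7 per arm, rounded up to 162, or 324 in total. Power at 162 per arm is 80.1%.

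The figure reproduces exactly, with no margin.

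**Step 2: what the 1.95 requires.** The 0.25 is 0.625 × 0.4, so 62.5% of the arm must show the full 0.4 in the analysed data. The other 37.5% are implicitly held at 2.2, which is also the average value they would receive under baseline carry-forward.

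**Step 3: missing scores among active participants.** Let m be the share of active participants without a follow-up score. The protocol gives no rate, so m is assumed. All 324 stay in the analysis and the difference becomes 0.25 × (1 − m), with SD kept at 0.8.

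| m | Difference | Power at 162 per arm |
|---|---|---|
| 0% | 0.25 | 80.1% |
| 2% | 0.245 | 78.5% |
| 5% | 0.2375 | 75.9% |
| 10% | 0.225 | 71.4% |
| 15% | 0.2125 | 66.4% |
| 20% | 0.20 | 61.2% |

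**Step 4: the favourable case.** If every missing intervention-arm outcome falls within the non-active 37.5%, the difference stays at 0.25 and power at about 80%. Missing controls scored at baseline stay at 2.2 on average and do not change the difference.

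**Step 5: if 62.5% means active and evaluated.** The 80% stands, but the participation needed is higher than 62.5%. If active participants go missing at rate m, it is 0.625 / (1 − m): 69% at m = 10%, 74% at 15% and 78% at 20%.

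**Step 6: baseline adjustment.** Adjusting for baseline SCL-10 reduces the residual SD to 0.8 × √(1 − r²), where r is the baseline to follow-up correlation. The protocol gives no r.

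- At an assumed r = 0.5, the residual SD is 0.8 × √0.75 = 0.693, and power with complete data is 89.9%. At r = 0.3 it is 83.6%; at r = 0.6 it is 93.9%.
- With baseline-value imputation, r = 0.5 and the residual SD held at 0.693, power is 83.0% at m = 10% and 73.6% at m = 20%.
- Carry-forward itself raises the correlation. With the same m throughout both arms it becomes 0.5 + 0.5m, that is 0.55 and 0.60, with residual SD 0.668 and 0.640. The formula then gives about 86% and 80%. A simulation that also allows for the extra spread from mixing active and non-active participants gives about 84% and 78%.
- A reasonable summary is 83 to 85% at 10% missing and 74 to 78% at 20%.
- Analysing observed cases only, at r = 0.5 and 20% loss (about 130 per arm), gives 82%. That figure does not apply under the rule in {20c}.

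**The case against.** The strongest reply is that nothing has been miscalculated. The paragraph claims 80% power under its own assumptions, and under them the claim is true. It also already discounts 37.5% of the intervention arm to no effect, and the 1.8 is tied to people who are evaluated as well as active. On that reading the allowance for missing outcomes is inside the 62.5%. Active participants attend sessions twice a week, eligibility requires weekly clinic follow-up, outcomes are collected at the local clinic and reminders are planned, so few active participants may go unmeasured. Missing-data detail is also deferred to an analysis plan that is not shown.

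Much of this stands. A reader might infer that the trial does not deliver 80% power, or that any missing outcome undermines it. The documents do not support that: missing controls and missing non-active participants leave the assumed difference intact. A reader might also infer that the protocol expects missing outcomes. The wording in {20c} is conditional and no rate appears anywhere.

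The reply does not settle what the 62.5% counts. The paragraph gives two conditions for the 1.8 and attaches the percentage to one of them. Deferral to an analysis plan does not resolve that, because the power, the number and the baseline-value rule are all fixed in this document.

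**Conclusion.** The point holds as a conditional one. The 324 is arithmetically correct and carries no margin. Its 80% power is assured only if 62.5% of the intervention arm are both active and measured. If the 62.5% means active only, power falls to about 76%, 71%, 66% and 61% when 5%, 10%, 15% and 20% of active participants lack a follow-up score. If missing intervention-arm outcomes all lie in the non-active share, it stays at about 80%.

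These figures rest on assumed missing rates, a common SD of 0.8, a control mean that stays at 2.2, and no baseline adjustment. Adjustment would recover the loss at about 10% missing, but at r = 0.5 it would not reliably do so at 20% while the baseline-value rule stands.

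The Discussion sentence on adequacy should not be read as a false guarantee. It can be taken to refer to the available patient population. Read as a statement about power, it depends on the same unstated condition.

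**What to change.** Keep 324 and change three places.

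1. **Sample size {14}:** state that 62.5% means active and evaluated. Otherwise, restate the power as 80% only if every active participant is measured, and put beside it the power at the expected missing rate under the final missing-data method.
2. **Section {20a}:** always adjust the primary Gaussian model for baseline SCL-10, whether or not it is imbalanced. Report the assumed correlation and the resulting power under the missing-data method that will actually be used.
3. **Discussion:** make the adequacy sentence conditional on the participation and measurement assumptions.

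The cost is a few sentences and one power calculation. No extra participants or measurements are needed, because SCL-10 is already collected at screening. The model change should be fixed in the detailed analysis plan that {20a} promises before data export.
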